### Study activities and interventions

ASCOT study activities can be broadly divided into: pilot trial activities and interventions with recruited people with TB and their households, which will gather data to support process evaluation; and complementary enhanced process evaluation activities with a subset of people with TB and key multisectoral stakeholders. 

**
*Pilot trial*
**

*Recruitment of people with TB and their households*

The ASCOT team will support BNMT DPCs, CHS, and FCHVs to recruit 128 people with TB across study sites. Participants will be identified prospectively during the recruitment period once they are diagnosed and notified to the NTP register. Participants will be invited to participate at their initial TB clinic visit, usually prior to initiation of treatment. They will then be randomised to a study arm at that clinic visit.

Household contacts of participants in social and socioeconomic study arms will be invited to participate in the social support activities using index-patient initiated invitations, which has been reported to be a preferred recruitment method for household studies in multiple settings
^
34–
36
^. Specifically, people with TB recruited to the study and randomised to the social or socioeconomic arms will be given an information leaflet and advised to inform their household members about the social support activities. As per WHO guidance, a household contact will be defined as “a person who shared the same enclosed living space for one or more nights or spent frequent or extended periods during the day with the index case during the 3 months prior to commencement of the current treatment episode”
^
37
^. Household contacts will also be given a separate PIS and asked to complete separate consent forms.

Participants will be free to withdraw from the study at any time by indicating this desire verbally and/or in writing to a member of the project team. Individual-level data from participants who withdraw will not be used further and will be securely deleted from project records. Deidentified group-level data collected during activities such as Focus Group Discussions, in which a participant who later withdraws from the study took part, will remain available for analysis.

*Household visits and surveys*

All participants will receive a household visit at three time points to complete the ASCOT survey:

**Visit one:** two to four weeks after TB treatment initiation, during the “intensive treatment phase”;

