The random number table will randomise participants 1:1:1:1 to the four study arms (social, economic, socioeconomic, and control arms) in blocks of 32 in each of the four study site districts according to site-level participant identification code. Once participants have given informed consent, been recruited, and given a site-level code, the ASCOT field team member who consented the participant will call the Project Manager (BR) and be informed by either KD or BR to which arm the participant has been allocated.

Digital randomisation using an online programme was originally considered but perceived as inappropriate and unfeasible in the study setting.

It will not be possible to blind participants or ASCOT field team members delivering the interventions (DPC, CHS, FCHV) to the randomisation. However, NTP staff will not be informed of the arm to which participants are randomised.

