### Outcomes to be measured

**
*Co-primary outcomes*
**

The co-primary outcomes of the ASCOT pilot trial are acceptability and feasibility of the social, economic, and socioeconomic support interventions.

*Feasibility* will be measured using quantitative data including:

i) Recruitment (e.g. number of people invited, recruited, and participant attrition);ii) Fidelity to survey completion and the intervention (e.g. adherence to and completion of socioeconomic support delivery including receipt of cash transfers and attendance at TB Club amongst intervention arm participants); andiii) ASCOT staff time and costs plus overall project costs.

*Acceptability* will be measured using mixed-methods including:

i) Quantitative analysis of the implementer and participant satisfaction form;iii) Thematic analysis of the qualitative FGD and KII data within Sekhon’s Framework for healthcare interventions and quantitative analysis of the brief questionnaire completed prior to FGDs will include evaluation of health systems readiness and scalability
^
50,
51
^.

**
*Secondary outcomes*
**

Unpowered, exploratory secondary outcomes will compare the proportion of people with TB in each study arm by rates of:

*TB treatment success:* NTP-defined outcome of completed TB treatment or confirmed cured documented in TB register.
*Catastrophic costs:* TB-affected households that incur total out-of-pocket expenses and lost income during TB illness that equated to more than 20% of the same household’s annual pre-TB income.
*Wellbeing:* measured by self-reported levels of stigma, depression, and quality of life at six-month follow-up adjusted for baseline.

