Quality of life will be assessed using the EQ-5D-5L index. EQ-5D-5L uses five dimensions of quality of life: mobility, self-care, usual activities, pain or discomfort, and anxiety or depression. Each question includes a five-category response scale from 1: no problem, 2: slight problem. 3: moderate problem, 4: severe problems, 5: being unable. The EQ-5D-5L has not been validated in Nepal but has been validated in neighbouring India. Since Nepal and India share common sociocultural conditions and geographical features, we will calculated quality of life scores from the Nepal data using the validated value sets and weightings from India as estimates. The EQ-5D-5L also includes a health rating covariate measured on a scale of 0 to 100 based on participants' self-reporting. The participants are asked to choose an appropriate point that best defines their health condition for that day and to label it with a mark on the scale printed in the survey with 0 indicating lowest/poorest health and 100 indicating highest/best health.

Descriptive statistics will be used to analyse the quantitative survey data collected during household visits. In line with our own and others’ related research, the arithmetic means and 95% confidence intervals of patient costs data that is continuous in distribution will be described regardless of the distribution of the data, and any direct expenses, lost income, or annual income recorded as “zero” or missing will be replaced with the mean cost of each costs category (unless >10% of data for a particular variable is missing)
^
5,
6,
53
^. Nepalese rupees, the local currency, will be converted to United States Dollars according to
OANDA rates at the time of data collection. Continuous stigma and quality of life data will be summarised by median and IQR or mean and SD depending on distribution. Categorical data will be summarised as proportions with 95% confidence intervals. Continuous data relating to costs, stigma, mental health, and quality of life scores (including self-rated health) will be compared across study arms where relevant using the Kruskal-Wallis test or one way ANOVA with p values <0.05 considered significant. Proportions of participants above and below the binary thresholds of treatment success, catastrophic costs, stigma, and depression will be summarised and compared across study arms where relevant using a Chi-2 test with p values of <0.05 considered significant.

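### The exploratory Wellbeing outcome is defined as baseline-adjusted, but the tests named for it are unadjusted and the only candidate baseline is surveyed after open allocation

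*Protocol article*

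**What the plan says.** Under Outcomes to be measured, Secondary outcomes, the protocol article defines Wellbeing as "measured by self-reported levels of stigma, depression, and quality of life at six-month follow-up adjusted for baseline". It introduces the secondary outcomes with "Unpowered, exploratory secondary outcomes will compare the proportion of people with TB in each study arm by rates of", so their exploratory status is explicit.

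Under Secondary exploratory outcomes analyses, continuous stigma, mental health and quality-of-life scores "will be compared across study arms where relevant using the Kruskal-Wallis test or one way ANOVA with p values <0.05 considered significant". For the dichotomised versions, "Proportions of participants above and below the binary thresholds of treatment success, catastrophic costs, stigma, and depression will be summarised and compared across study arms" by a Chi-2 test at the same threshold. The section mentions no regression, analysis of covariance or change from baseline.

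On timing, Recruitment of people with TB and their households states: "Participants will be invited to participate at their initial TB clinic visit, usually prior to initiation of treatment". The next sentence reads: "They will then be randomised to a study arm at that clinic visit". Household visits and surveys places the first of three surveys "two to four weeks after TB treatment initiation" and the last at 20 to 24 weeks. Randomisation and blinding says that the field worker who took consent learns the arm by telephone, and that neither participants nor the field staff delivering support can be blinded.

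**The concern.** There are two linked problems.

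First, the outcome definition and the analysis section disagree. One promises a six-month comparison adjusted for the starting level. The other fixes tests that, applied to the scores and thresholds as described, make no such adjustment. A report could follow either section and claim to have followed the protocol.

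Second, there is no true baseline to adjust for. Stigma, depression and quality of life are self-reported, and are first recorded after participants and field staff know who is to receive cash, clubs, both or neither. A score taken then may already carry part of the effect of allocation.

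The comparison is exploratory, so no primary conclusion is at stake. It matters because a stated aim of the pilot is to inform a larger trial, whose longer-term outcomes include reduced self-stigma and better mental wellbeing. The same baseline timing and tests could be carried into that design.

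**Working it through.** The plan gives no figure on this point to reproduce. The check sets the sections side by side and then sizes the consequences under stated assumptions.

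**Definition against analysis.** The Wellbeing definition calls for baseline adjustment. The analysis section applies Kruskal-Wallis or one-way ANOVA to the scores and Chi-2 to the binary thresholds. None of these takes a covariate, and no change score is described. The two sections cannot both be followed.

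**Order of events.**
- Consent and randomisation: initial clinic visit, usually before treatment.
- Arm disclosed: by telephone, once consent is given and a site code assigned.
- First survey: two to four weeks after treatment starts.
- Last survey: 20 to 24 weeks after treatment starts.

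Where randomisation precedes treatment, the first score comes at least two weeks after open allocation. The Abstract puts the first survey at 0 months, which does not match the two to four weeks in the body, but nowhere is a survey placed before randomisation. The two-week wait is justified by questions on the socioeconomic impact of a treatment phase. That gives no reason to delay these three scales.

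**Consequence A: the analysis is run unadjusted, as written.** From the protocol: 32 per arm and a 0.05 threshold, taken here as two-sided. Assumed: correlation r between a true baseline and the six-month score, and an effect of 0.5 SD. Adjustment multiplies the residual variance by 1 − r², so the equivalent arm size is 32/(1 − r²). For one pairwise comparison, the difference detectable with 80% power is (1.960 + 0.842) × √(1 − r²) × √(2/32) SD.

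| r (assumed) | 1 − r² | 32/(1 − r²) | Detectable difference (SD) | Power at 0.5 SD |
|---|---|---|---|---|
| 0 (unadjusted) | 1.00 | 32 | 0.70 | 0.52 |
| 0.3 | 0.91 | 35.2 | 0.67 | 0.55 |
| 0.5 | 0.75 | 42.7 | 0.61 | 0.64 |
| 0.7 | 0.51 | 62.7 | 0.50 | 0.80 |

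The precision forgone is therefore 9% to 49% of the variance.

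**Consequence B: visit one is used as the covariate.** Let f be the share of the six-month effect already present at visit one, in the same direction, and let b be the covariate slope (equal to r when both scores have the same SD). The expected adjusted estimate is (1 − b × f) of the true effect.

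| b (assumed) | f = 0 | f = 0.1 | f = 0.25 | f = 0.5 |
|---|---|---|---|---|
| 0.3 | 1.00 | 0.97 | 0.925 | 0.85 |
| 0.5 | 1.00 | 0.95 | 0.875 | 0.75 |
| 0.7 | 1.00 | 0.93 | 0.825 | 0.65 |

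A simulation with 32 per arm at b = 0.5 and f = 0.25 gave 0.88, against 0.875 from the formula. The loss runs from 0 to 35%.

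A and B are alternatives. A applies if the model is unadjusted, B if it is adjusted for visit one.

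**The case against.** The strongest reply is that the protocol calls these outcomes unpowered and exploratory. Feasibility and acceptability are co-primary, and no progression rule or sample-size calculation rests on Wellbeing. That stands, and it limits the weight of the point.

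A reader might infer that the late baseline biases the planned analysis. The documents do not support this: the tests as written compare six-month results between randomised groups and do not use the visit-one score. Shrinkage arises only if that score is brought into the model.

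A reader might also infer that arm-specific support has begun by visit one. This is not stated. The education and nutrition package at an initial household visit goes to every arm, and the arm-specific activities are in a figure that is not shown. What the text does establish is knowledge of allocation.

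It can be said that one-way ANOVA or Kruskal-Wallis on change from visit one would be a crude baseline adjustment. That is correct in principle, so the tests do not rule adjustment out. But the section describes comparing the scores, not changes, and a change from visit one would subtract the whole of any early effect (share f) rather than b × f.

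Finally, the conflict might be left to a fuller analysis plan. Missing detail could be, but here the article itself fixes tests that disagree with its own outcome definition.

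**Conclusion.** The point holds as a contradiction between the outcome definition and the analysis section, combined with the absence of any measure taken before allocation. It should be fixed. It does not threaten the trial's main conclusions, and the co-primary outcomes are unaffected.

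The size rests wholly on assumptions, because the document gives no correlation, effect size or early effect. Following the written tests leaves the comparison free of bias from the late baseline, at the price of the precision that a true baseline would have bought. Adjusting for visit one may cost nothing or about a third of the effect, depending on how much of it is already present by then. An early effect in the opposite direction would inflate the estimate instead.

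**What to change.** 1. Make the Wellbeing definition and the analysis section agree on one model: linear regression of the six-month score on arm and site, with logistic or risk-difference regression for the binary stigma and depression thresholds. Report between-arm differences with 95% confidence intervals (odds ratios if logistic). Site belongs in the model because allocation is blocked within district.
2. Let a baseline score enter the main model only if it was recorded before allocation was disclosed. Otherwise remove baseline adjustment from the main definition, describe visit one as an early post-randomisation measure, and report the visit-one-adjusted model as a labelled sensitivity analysis.
3. Reconcile the Abstract's 0-month survey with the two to four weeks in the body.
4. In the follow-on trial, collect the three scales at consent, before the allocation call, and leave the cost questions at the household visit.

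Items 1 to 3 are changes of wording and cost nothing in data collection. Item 4 costs a few interview minutes per participant. It cannot be applied here, because Study status reports that recruitment ran until September 2022.

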### Data collection and management

**
*Survey and pilot trial*
**

During the survey, information will be collected by the project team during household visits. This information includes but is not limited to socioeconomic, health, psychosocial, and behavioural data. The data of consenting TB patients will subsequently be linked with data from NTP’s TB patient register as part of its routine surveillance data collection in each study site. This data will be collected through use of tablets and/or paper depending on the local situation (e.g. security and feasibility in each district). When entered digitally, results will be entered into a mobile data collection tool via the Commcare – ODK platform (Dimagi, Inc., Boston, MA), which is based on open-source suite of tools called Open Data Kit/OpenRosa developed at the University of Washington's Department of Computer Science and Engineering. The data will be uploaded to secure cloud-based servers hosted by Dimagi. Dimagi servers are secure and HIPAA compliant.

**
*Process evaluation including FGDs, KIIs, and workshop*
**

The multisectoral stakeholders identified by the scoping exercise (and also including a subset of purposively sampled people with TB who participated in the survey) will complete a short pre-FGD/KII questionnaire (in person, by post, or by email) and then participate in either an FGD or KII. FGDs and KIIs will be audio-recorded.

All patient data and FGD/KII results will be entered into an encrypted access database on a project computer, which will remain at BNMT secure offices at all times. The data will be uploaded to a LSTM password-secured server.

Following discussions among the ASCOT project team and during TSC meetings, it was decided that a Data Monitoring Committee was not required for this pilot acceptability and feasibility trial with a relatively small sample size. However, a Data Monitoring Committee will be formed for any follow-on large-scale, well-powered trial assessing effectiveness of the intervention on catastrophic costs incurrence and TB treatment outcomes.

Primary study data will be managed by the Data Manager of Birat Nepal Medical Trust. Data input, cleaning, checking and double-checking, and management will be iterative and ongoing throughout the study. Data will be checked for consistency and completeness by the Data Manager and ASCOT Project Manager and double-checked by the Chief Investigator prior to hand-off to LSTM. This data will be exported to Stata and transferred to LSTM servers for analysis. PIS will be provided and written informed consent will be obtained from all study participants. Secondary data obtained from patient register records and other sources of the Nepal NTP will be copied and entered in an electronic database by BNMT staff.

Specifically, audio recordings from the FGDs will be stored in a password-protected digital folder on an LSTM secure server. Only the Chief Investigator, Project Manager, and transcribers will have access to the data. Audio-recording data will be stored for seven years, as per the requirement of the BNMT’s data policy, after which they will be deleted.

Paper-based copies and study documents will be stored in the locked offices of BNMT. The electronic database will be stored in files within LSTM’s secure server and will be password protected. Any tablet devices used for data entry will be password protected and data will be uploaded to LSTM’s secure server weekly. Access to final data will be limited to the Chief Investigator, Data Manager, Project Manager, and key authorised ASCOT staff.

### Data analysis and statistical plan

**Co-primary outcome analyses**

**
*Feasibility*
**

Target versus observed participant recruitment, completed cash transfers, completed TB Club attendance, and attrition from follow-up at each survey time point will be reported across study arms using the CONSORT flow diagram, summarised using proportions and percentage rates, and where relevant compared across study arms using a Chi-2 test with p values of <0.05 considered significant.

ASCOT staff and project costs will be summated for the project as a whole and also as total and mean costs by specific project activities (i.e. TB Clubs, home visits, cash transfers). The latter will support generation of estimates of the costs to deliver a single unit activity such as a TB Club or Cash Transfer. Continuous costs data will be summarised by median with interquartile range or mean with standard deviation depending on the distribution of the data. Total ASCOT staff and project costs will be compared across study arms using the Kruskal Wallis test or one way ANOVA with p values of <0.05 considered significant.

**
*Acceptability*
**

Quantitative data from implementer and participant feedback forms detail the respondents’ ratings on the provision of ASCOT project activities received including recruitment, TB information and education, home visit, TB club, and cash transfers. Responses are provided in 5-point Likert Scale including 1 “Very bad”, 2 “Bad”, 3 “Neither good nor bad”, 4 “Good”, and 5 “Very Good”. Responses will be summarised using proportions and rates of response by category. Proportions of respondents reporting “Good” and “Very good” in each category will be aggregated and compared across study arms where relevant using a Chi-2 test with p values of <0.05 considered significant.

Qualitative data will be analysed by applying thematic analysis within Sekhon’s framework of healthcare interventions
^
51
^ and also application to the NoMAD tool’s
^
49
^ four constructs (coherence, engagement, collective action, and reflexive monitoring) using NVivo 12 to manage the data
^
52
^. Initial codes will be generated, which will be updated as further data becomes available and collated following each successive FGD and KII respectively. Both open and closed first-order category will be used to label data within NVivo with specific a priori consideration of codes relating to health system readiness and intervention scalability. Codes may then also be grouped together into second-order and third-order themes. After all the transcripts are coded and analysed, to increase trustworthiness, we will independently review coding and themes and refine and triangulate them through further debate and discussion where necessary
^
18
^.

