NTP managers (n=5)Social protection decision makers (n=5)ASCOT District Program Coordinators (DPCs) (n=5)

Inclusion criteria for the process evaluation participants are: aged 18 years or older; identified by scoping review or, if a person with TB participated in ASCOT pilot trial whether recruited by ACF or PCF; able to provide written, informed consent (or thumb print if unable to write).

Exclusion criteria for the process evaluation participants are: under 18 years of age; not identified by scoping review or, if a person with TB did not participate in ASCOT pilot trial; and unable to provide written, informed consent or thumb print.

**
*Sample size and statistical power*
**

A sample of ≥40 people is recommended for pilot trials and process evaluations
^
31
^ and ~100 people for TB patient costs data
^
32
^. Our previous research in the study site attained recruitment rates of >90% of those invited, attrition during follow-up was less than 5%, and we anticipate similar rates during the ASCOT project
^
15
^. We have budget allowance for minor coronavirus disease 2019 (Covid-19) under-recruitment or attrition and plan to continue recruitment of people with TB until we recruit 128 participants to ensure the sample size of 100 with complete data available is met.

Information power (saturation) is estimated to be reached at 25 FGD and 15 KII participants
^
33
^. Purposive selection of participants and implementers for FGDs and KIIs will ensure gender, district, poverty, and NTP/project role diversity. Previous uptake of FGDs and KIIs was good but we will invite approximately 50 stakeholders as contingency.

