**Figure 7. f7:**
[figure not shown]
Intervention activities conducted in each study arm. Abbreviations: ASCOT = the “Addressing the Social Determinants and Consequences of Tuberculosis” project; IEC = Information, Education, and Counselling; NTCC = Nepal National Tuberculosis Control Centre; TB = tuberculosis; UCT = unconditional cash transfer.

Following refinements by BNMT team and TSC inputs, recruitment will proceed. Again, when a study site reaches 32 recruited participants, recruitment will discontinue in that district. This provides ample allowance for completion of intervention activities and three surveys in 32 participants given the predicted attrition rate of ≤10% in the study sites.

The longitudinal survey data detailing participant feedback will form part of the process evaluation of the acceptability and feasibility of the ASCOT intervention. This will be supplemented by real-time self-reported ASCOT project feedback, and time and expense diaries of BNMT implementers, including DPCs and CHS. This data will be further complemented by the enhanced process evaluation aiming to evaluate health systems readiness and scalability of the ASCOT intervention. 

There will be multiple opportunities during the implementation of the pilot trial to assess for any harms or adverse effects. First, the longitudinal survey includes questions related to feedback from participants on the interventions received and involvement in the ASCOT project. Second, after each TB Club is conducted, participants will be asked to provide verbal and written feedback on the activities undertaken during the TB Club, including whether they perceive any of the activities to have caused harm or have the potential to cause harm. Third, issues relating to harm or adverse effects of the ASCOT project are included in the topic guides for KIIs and FGDs. All of these data will be analysed in real-time during the project and discussed between the ASCOT project team and where necessary the TSC to identify if any remediating actions are required. The criteria for discontinuing interventions include: participants who withdraw from the ASCOT project who, as an individual and inclusive of their household, will no longer receive the intervention; harm or adverse effect is identified that is felt by the project team and TSC to preclude continuation of interventions; and acts of God or unforeseen cuts to the study budget curtailing project activities.

**

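### The between-arm p-value on total costs is uninformative on either reading, and the co-primary feasibility proportions carry no measure of uncertainty

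*Protocol article*

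**What the plan says.** Under Outcomes to be measured, "The co-primary outcomes of the ASCOT pilot trial are acceptability and feasibility of the social, economic, and socioeconomic support interventions". The quantitative feasibility measures cover recruitment and attrition, fidelity (including "receipt of cash transfers and attendance at TB Club amongst intervention arm participants"), and "ASCOT staff time and costs plus overall project costs".

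The Feasibility part of Co-primary outcome analyses then sets out two analyses.

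- **Proportions.** "Target versus observed participant recruitment, completed cash transfers, completed TB Club attendance, and attrition from follow-up at each survey time point will be reported" by arm in a CONSORT flow diagram, summarised as proportions and percentage rates, and "where relevant compared across study arms using a Chi-2 test with p values of <0.05 considered significant".
- **Costs.** Staff and project costs are added up for the whole project and by activity, to give unit costs for a TB Club or a cash transfer. Continuous cost data are summarised by median and IQR or by mean and SD. Then "Total ASCOT staff and project costs will be compared across study arms using the Kruskal Wallis test or one way ANOVA", again at p<0.05. Unlike the Chi-2 sentence, this one is not limited to relevant comparisons.

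The planning values are 128 recruited (32 per arm and 32 per district), 100 with complete data, and more than 90% of those invited recruited. Attrition appears twice. In Sample size and statistical power, earlier research in the study site is cited in which "attrition during follow-up was less than 5" per cent, with similar rates anticipated. Under Study arms and activities, 32 participants per district are called ample "given the predicted attrition rate of ≤10% in the study sites".

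**The concern.** Whether a support package is feasible is a question about levels: are enough people recruited, is enough of the support delivered, are enough people retained, and at what cost? A test of homogeneity between arms does not address levels. It can be silent when every arm does badly and loud when overall performance meets expectation.

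For costs the difficulty is sharper. Arms that receive cash and TB Clubs must cost more than an arm that receives neither, so rejecting equality tells the team nothing. What the future trial needs is the size of each cost and what it is made of.

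At stake is how the pilot's co-primary result will be read. With p<0.05 as the only inferential rule, a non-significant comparison may be written up as reassurance, and point estimates from 32 to 128 people may be taken forward as if they were exact.

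**Working it through.** **Inputs.** Four arms, 1:1:1:1, 32 each (Abstract): 4 × 32 = 128, which reproduces the stated sample size. Districts are randomised in blocks of 32, so 32 / 4 = 8 per arm per district (Randomisation and blinding). Attrition is below 5% or at most 10% (sections above). No power or effect size is stated for any feasibility test, so there is no such figure to reproduce.

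**1. Cost test, one total per arm.**
- One-way ANOVA: residual df = 4 totals − 4 arms = 0. There is no F statistic or p-value.
- Kruskal-Wallis: the ranks are 1, 2, 3, 4, one per arm. H = 12 / (4 × 5) × (1 + 4 + 9 + 16) − 3 × 5 = 18 − 15 = 3.0. On 3 df, p = 0.392. The order and spacing of the totals do not enter, so the test can never reach 0.05.

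**2. Cost test, apportioned costs.** Replicates now exist and both tests run. As an illustration, suppose the arms' costs do not overlap.
- With 4 district totals per arm the rank sums are 10, 26, 42 and 58. H = 12 / (16 × 17) × (100 + 676 + 1764 + 3364) / 4 − 3 × 17 = 65.12 − 51 = 14.12, p = 0.0027.
- With 32 participant-level costs per arm, H = 119.07, p about 1e-25.

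Transfers go only to the economic and socioeconomic arms, and TB Clubs only to the social and socioeconomic arms. Separation is therefore expected, and the p-value mainly reflects how finely costs were apportioned.

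**3. Chi-2 test against the feasibility question.**
- If every arm completes 29/32, or 16/32, or 6/32, observed equals expected in every cell: statistic 0, p = 1.0 in all three cases. Good and very poor delivery give the same result.
- With losses of 0, 0, 0 and 6, the overall rate is 6/128 = 4.7%, inside both attrition expectations. Expected losses are 6/4 = 1.5 per arm and expected retained 30.5. Statistic = (3 × 1.5² + 4.5²) / 1.5 + (3 × 1.5² + 4.5²) / 30.5 = 18.00 + 0.89 = 18.89 on 3 df, p = 0.0003.
- Expected counts of 1.5 make that p-value approximate. Six losses in one arm is the most extreme table, so the exact value is 4 × C(32,6) / C(128,6) = 4 × 906,192 / 5,423,611,200 = 0.0007. The conclusion is the same.

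**4. What an interval would show.** Wilson 95% limits: [p + z²/2n ± z√(p(1−p)/n + z²/4n²)] / (1 + z²/n). For 6/128: (0.0469 + 0.0150 ± 0.0396) / 1.0300 = 2.2% to 9.8%.

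| Illustrative count | Estimate | Wilson 95% CI |
|---|---|---|
| 6/128 lost | 4.7% | 2.2% to 9.8% |
| 13/128 lost | 10.2% | 6.0% to 16.6% |
| 58/64 delivered (the two arms receiving a component) | 90.6% | 81.0% to 95.6% |
| 29/32 delivered (one arm) | 90.6% | 75.8% to 96.8% |

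**5. Comparison within the document.** Secondary exploratory outcomes analyses plans 95% confidence intervals for categorical data. The co-primary feasibility proportions have none stated.

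**6. Recruitment.** Randomisation follows consent and recruitment, and the blocks fix 8 per arm per district. Uptake is therefore a single overall proportion and cannot be compared by arm.

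**The case against.** The strongest reply is that feasibility is not judged by tests alone. The sentence containing the Chi-2 test begins with a target-versus-observed report, the test is limited to relevant comparisons, and absolute benchmarks exist. This stands. A reader might infer that poor retention in every arm would pass unnoticed, but the document does not support that. At 30% loss, for example, 128 × 0.70 is about 90 people, visibly short of the 100 with complete data.

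A second reply is that the cost test need not use arm totals. The plan to summarise costs by IQR or SD, and the implementers' time and expense diaries, suggest replicate records, and an unseen full protocol or SAP may define the unit. This also stands, so it would be wrong to say that the test cannot be computed on any reading. Only ANOVA on arm totals fails outright. The point does not rest on an undefined unit, because defining it would only move the test from step 1 to step 2.

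A third reply concerns small cells. Expected losses of 32 × 0.05 = 1.6 to 32 × 0.10 = 3.2 per arm might suggest an invalid Chi-2 test. Simulation puts its true size at about 3.3% and 4.2%, so it is only mildly conservative. Power is low: 51% to flag one arm at 20% attrition against 5% in the others, and 27% at 15%. That is ordinary for 32 per arm and is no fault in itself.

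Finally, it is tempting to extend the small-cell remark to treatment failure, given success above 90%. Treatment success is an exploratory secondary outcome that the protocol itself labels unpowered, so it has no place in a point about feasibility.

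**Conclusion.** The point holds in two parts.

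1. The significance test on total staff and project costs is uninformative whichever unit is meant: undefined (ANOVA) or fixed at p = 0.39 (Kruskal-Wallis) on arm totals, and a test of a difference built into the design on apportioned costs.
2. The co-primary feasibility proportions have a descriptive target-versus-observed report, but no stated measure of uncertainty. Their only inferential rule answers a different question, with p = 1.0 under equal failure and p = 0.0003 at 4.7% overall loss.

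The consequence is for interpretation of a co-primary outcome. Conduct, sample size and data collection are unaffected. The conclusion assumes 32 per arm as planned; the counts in the worked examples are illustrative.

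**What to change.** - **Costs.** Delete the between-arm significance test. Report cost per participant by arm, with cash value separated from staff time, alongside the unit-activity costs already planned.
- **Proportions.** Give Wilson or exact 95% confidence intervals for survey completion and attrition, overall and by arm; for transfers delivered and TB Club attendance, in the arms that receive them; and for uptake, overall only. This matches what the protocol already plans for exploratory categorical data.
- **Reference values.** Read the intervals against the protocol's own planning values: 128 recruited, 100 with complete data, more than 90% of those invited recruited, and a single attrition figure. Below 5% and at most 10% do not strictly contradict each other, but they are different yardsticks and should be reconciled.
- **P-values.** Treat any between-arm p-value on feasibility measures as descriptive.

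The cost is a change of analysis wording and slightly more reporting, with no new data. The downside is that a missed planning value becomes visible.
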